**PROTOCOL SYNOPSIS**

| **Sponsor legal name** | African Malaria Network Trust |
| --- | --- |
| **Finished product** | MSP 3 LSP malaria vaccine |
| **Active ingredient** | MSP 3 [181-276) LSP |
| **Trial Title:** | A double blind, randomized, controlled, dose escalation phase Ib field trial in 12 to 24 month old children in Burkina Faso to evaluate the safety and immunogenicity of the *Plasmodium falciparum* Merozoite Surface Protein-3 Long synthetic peptide (MSP 3) adjuvanted in aluminium hydroxide versus hepatitis B |
| **Trial Identifier:** | **MSP 3_BF_0302** |
| **Clinical phase** | Phase 1b |
| **Principal**  **Investigator** | [name] [name], BA, MD, PhD |
| **Investigators** | [name] MD  [name], PhD  [name]  [name], Pharm D, MSc  [name] Pham D, MSc  [name] Pharm D |
| **Biological**  **Evaluators**  **Biological supervisor** | [name], PhD  [name] MSc. |
| **Trial Centre(s)** | **Centre National de Recherche et de Formation sur le Paludisme**  [name]  BURKINA FASO  [contact] [contact] |
| **Planned Trial**  **Period** | March 2007 to February 2008 |
| **Primary Objective** | **To assess the safety and reactogenicity** of 3 doses of 15 µg and 30 µg MSP3 adjuvanted in aluminium hydroxide given at D0, D28 and D56 in healthy children aged 1-2 years old in Burkina Faso on the following :   1. Solicited adverse events    - immediate reactogenicity (within 1 hour, with emphasis on allergic reactions),    - local and systemic reactogenicity during 7 days following the vaccine injection (day of vaccination and 6 consecutives following days) 2. Unsolicited adverse events occurring within 28 days following each vaccination 3. Serious adverse events (SAE) whenever it occurs during the trial period (from first visit to last visit). |
|  |  |
| **Secondary**  **Objective** | **To assess the humoral immune response** to the vaccine antigen by measuring the increase in the level of antibodies **through measuring:**  IgG, IgM and IgA to MSP3-LSP and peptides a, b, c and d of MSP3  Isotypes IgG1, IgG2, IgG3, IgG4, (MSP3-LSP peptide)  Using ELISA, before and four weeks after each vaccination, as well as 4 months after the last injection and one year after the first injection (D0, D28, D56, D84, D168 and D365)  **To assess the cellular immune response to the vaccine antigens by measuring:**  The number of cells producing IFNγ by Elispot to MSP3-LSP and peptides a,b,c and of MSP3 before and four weeks after the second and the third injection as well as four months after the last injection (D0, D56, D84 and 168) |
| **Exploratory Objective(s)** | To evaluate IgG ability to recognise the native protein on Merozoite by using Western Blot (WB) method before the first injection and four  Weeks, four month and one year after the last injection (D0, D84, D168 and D365)  To evaluate functionality of IgG by using the ADCI technique on D0, D84 D168 and D365 (only if isotype study shows the production of MSP3 specific cytophilic Abs in > 30% of volunteers) |
| **Trial Design** | Randomised, controlled, single trial centre |
| **Planned Sample**  **Size** | The total number of participants will be 45 allocated in two groups as following:   - 22 participants in the full dose (the 30µg of MSP3) or control vaccine group (group 1) - 23 participants in the half dose (15µg of MSP3) or control vaccine group (group 2) |
| **Inclusion Criteria** | 1. Children aged 1-2 years old 2. Healthy by medical history and physical examination 3. Signed Informed Consent by guardian/parent 4. Resident in the study area village during the whole trial period |
| **Non-Inclusion**  **Criteria** | 1. Symptoms, physical signs of disease that could interfere with the interpretation of the trial results or compromising the health of the subjects 2. Immunosuppressive therapy (steroids, immune modulators or immune suppressors) within 3 months prior recruitment. (for corticosteroids, this will mean prednisone, or equivalent,  0.5 mg/kg/day. Inhaled and topical steroids are allowed.) 3. Cannot be followed for any social, psychological or geographical reasons. 4. Use of any investigational drug or vaccine other than the study vaccine within 30 days preceding the first dose of study vaccine, or planned use up to 30 days after the third dose. 5. Suspected or known hypersensitivity to any of the vaccine components or to previous vaccine. 6. Laboratory abnormalities on screened blood samples out of range, more specifically refer to table 2. 7. Planned administration of a vaccine not foreseen by the study protocol within 30 days before the first dose of vaccine. An exception, is the receipt of an EPI or licensed vaccine (measles, oral polio, Hib, meningococcal and combined diphtheria/pertussis/tetanus vaccines) which may be given 14 days or more before or after vaccination 8. Evidence of chronic or active hepatitis B infection 9. Presence of chronic illness that, in the judgement of the investigator, would interfere with the study outcomes or pose a threat to the participant’s health. 10. Administration of immunoglobulin and/or any blood products within the three months preceding the first dose of study vaccine or planned administration during the study period 11. History of surgical splenectomy. 12. Moderate or severe malnutrition at screening defined as weight for age Z-score less than ‑2 |
| **Investigational Product** | MSP 3 [181-276] LSP |
| ***Form*** | Adjuvanted with Alhydrogel in lyophilised form |
| ***Dose*** | 30µg or 15µg |
| ***Route*** | Subcutaneous, alternate deltoid region |
| **Control Product** | Hepatitis B |
| **Vaccination**  **Schedule** | Primary immunisation : day 0, 28; and 56 |
| **Follow-up duration** | One year after the first vaccination |
| **Blood sampling Schedule** | **D-28: (**screening)  **D0, D28 and D56**: (immediately before each vaccination)  **D84:** (28 days after third vaccination)  **D168:** (4 months after last vaccination)  **D 365:** (1 year after first vaccination) |
| **Primary**  **Evaluation Criteria** | The primary endpoints are measures of the safety and reactogenicity of the vaccine as determined by:   1. Occurrence of solicited symptoms during a 7 day follow-up period after each vaccination (day of vaccination and 6 consecutives days) 2. • Occurrence of unsolicited symptoms during a 28 day follow-up period after each vaccination 3. • Occurrence of serious adverse events throughout the study period |
| **Secondary Evaluation Criteria** | 1. **Humoral response to vaccine antigens:**   Post vaccination levels of IgG, IgA and IgM, expressed in arbitrary units (ng/ml), relative to the pre-vaccination level (D0): D28/D0, D56/D0, D84/D0, D168/D0, and D365/D0.   1. **Cellular immune response to vaccine antigens:**   The number of cells producing IFNγ by Elispot expressed in number of spots /106 cells |
| **Exploratory Evaluation Criteria** | **To evaluate IgG ability to recognise the native protein on Merozoite by using WB**   - **Parasite inhibition by ADCI (SGI %) on D0, D84, D168 and D365. (only if isotype study shows the production of MSP3 specific cytophilic Abs in > 30% of volunteers)** |
| **Statistical Methods** | The analysis shall be descriptive  The final analysis is planned 1 month post Dose 3 to evaluate whether the safety GO/No GO criteria are met to proceed to a phase 2b in. An annex safety analysis will be performed at the end of the study, 9 months post Dose 3. |

| Study phases | Screening | Vaccination Phase (Double blind) | | | | | | | | | | Follow up (Single blind) | | |
| --- | --- | --- | --- | --- | --- | --- | --- | --- | --- | --- | --- | --- | --- | --- |
| Clinic Visit | **V1** | **V2** |  | **V3** | **V4** |  | **V5** | **V6** |  | **V7** | **V8** | **V9** |  | **V10** |
| **Home visits1** |  |  | **HV1-5** |  |  | **HV6-10** |  |  | **HV11-15** |  |  |  | **HV16-21** |  |
| **Trial Timelines (Days,)** | **D-28** | **D0** | **D1-D5** | **D6** | **D28** | D29-D35 | **D36** | **D56** | **D57-D62** | **D63** | **D84** | **D168** | **D196-D337** | **D365** |
| **Time Windows (Days)** |  |  4 D |  |  |  4 D |  |  |  4 D |  |  |  4 D |  7 D |  7 D |  14 D |
| **Study procedures** |  |  |  |  |  |  |  |  |  |  |  |  |  |  |
| Screening consent |  |  |  |  |  |  |  |  |  |  |  |  |  |  |
| Study Consent |  |  |  |  |  |  |  |  |  |  |  |  |  |  |
| Check of inclusion /non Inclusion Criteria |  |  |  |  |  |  |  |  |  |  |  |  |  |  |
| Medical History |  |  |  |  |  |  |  |  |  |  |  |  |  |  |
| Worm infestation treatent |  |  |  |  |  |  |  |  |  |  |  |  |  |  |
| Physical Examination |  |  |  |  |  |  |  |  |  |  |  |  |  |  |
| Check of contra-Indications to vaccination |  |  |  |  |  |  |  |  |  |  |  |  |  |  |
| Randomisation |  |  |  |  |  |  |  |  |  |  |  |  |  |  |
| Vaccine administration |  | **** |  |  | **** |  |  | **** |  |  |  |  |  |  |
| Check of elimination criteria |  |  |  |  |  |  |  |  |  |  |  |  |  |  |
| Recording of medication |  |  |  |  |  |  |  |  |  |  |  |  |  |  |
| **Safety and reactogenicity data collection** |  |  |  |  |  |  |  |  |  |  |  |  |  |  |
| Immediate post-vaccine surveillance (60’) |  | x |  |  | x |  |  | x |  |  |  |  |  |  |
| Recording of solicited Local & Systemic Events/Reactions |  |  | x | x | x | x | x | x | x | x |  |  |  |  |
| Recording of unsolicited adverse events |  |  |  |  |  |  |  |  |  |  |  |  |  |  |
| Recording of Serious Adverse Events |  |  |  |  |  |  |  |  |  |  |  |  |  |  |
| **Laboratory analysis** |  |  |  |  |  |  |  |  |  |  |  |  |  |  |
| Complete blood count |  |  |  |  |  |  |  |  |  |  |  |  |  |  |
| Creatinine, ALT/AST, Biluribin |  |  |  |  |  |  |  |  |  |  |  |  |  |  |
| Humoral response measurement |  |  |  |  |  |  |  |  |  |  |  |  |  |  |
| Cell mediated immunity measurement |  |  |  |  |  |  |  |  |  |  |  |  |  |  |
| Functional assays (ADCI) |  |  |  |  |  |  |  |  |  |  |  |  |  |  |
| Anti-HBs antibodies |  |  |  |  |  |  |  |  |  |  |  |  |  |  |
| Western blot |  |  |  |  |  |  |  |  |  |  |  |  |  |  |
| **Analysis and reporting** |  |  |  |  |  |  |  |  |  |  |  |  |  |  |
| Final Analysis |  |  |  |  |  |  |  |  |  |  |  |  |  |  |
| Annex safety Analysis |  |  |  |  |  |  |  |  |  |  |  |  |  |  |

**1**  from the first home (HV1) to HV15 the visit will be daily. The visits wil be monthly from HV16 to HV21

| **List of Abbreviations** |
| --- |

95% CI 95% Confidence Interval

AIDS Acquired Immunodeficiency Syndrome

AMANET African Malaria Network Trust

ADCI  Antibody Dependent Cellular Inhibition of parasite growth assay

CRF  Case Report Form

CNRFP Centre National de Recherche et de Formation pour le Paludisme

CTA Centre des Traitements Ambulatoires

DSMB Data and Safety Monitoring Board

EC  Ethics Commitee

ELISA Enzyme Linked Immuno Sorbent Assay

EMVI European Malaria Vaccine Initiative

GCP Good Clinical Practice

GMC Geometric Mean Concentration

GPT Glutamic-Pyruvic Transaminase

HBV  Hepatitis B Virus

HCV  Hepatitis C Virus

HIV Human Immunodeficiency Virus

IgG Immunoglobuline G

INF  Interferon 

MCHC Mean Corpuscular Hemoglobin Concentration

MCH Mean Corpuscular Hemoglobin

MCV Mean Corpuscular Volume

MSP3 Merozoite surface Protein 3

RBC  Red Blood Cells

RESA Ring Erythrocyte Surface Antigen

SAE  Serious Adverse Events

SOP  Standardised Operating Procedure

SGOT Serum Glutamic Oxaloacetic Transaminase

WB Western Blot

WBC White Blood Cells

WHO World Health Organization

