### Parameters to be measured

The levels of IgG and IgM will be expressed as concentration (ng/ml). The sero-response will be defined in the post-vaccination to re-vaccination ratio. (D28/D0, D56/D0, D84/D0, D168/D0, and D365/D0).

Because of the prior natural exposure of trial subjects to Plasmodium falciparum and so to MSP3 antigen, it is anticipated that almost all participants will be sero-positive before vaccination occurs. Consequently, the sero-conversion rate, defined as the number of pre-vaccination sero-negative candidates having a concentration considered as positive after vaccination, will not be used.

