### Antibody Dependant Cytophilic Inhibition

The functionality of IgG shall be assessed by using the Antibody Dependant Cytophilic Inhibition (ADCI) technique.

The assays for assessing functionality of immune responses will be done on samples obtained on the following days: D0, D84, D168 and D365

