## Sample size considerations

The trial sample size will be determined on the primary evaluation criteria, concerning the occurrence of systemic adverse events. The total sample size is calculated at 45 children to be distributed as shown in the table below:

| 1-2 Year Olds |
| --- |
| 15 receiving 15µg MSP 3 vaccine |
| 15 receiving 30µg MSP 3 vaccine |
| 15 receiving Hepatitis B vaccine |
| **45 Children in total** |

The hypothesis in absolute terms has the following assumptions considered:

The lost of follow-up or protocol deviation is anticipated to be no more than 10%. Therefore with a total sample size of 45, the study is adequately powered to show such a difference if the assumptions hold.

With 14 children completing follow-up in each MSP3 arm, the study will be have 90% power to detect at least one MSP3 vaccinated individual with a systemic reaction (or a serious adverse event) if the underlying risk of such an event is 15% or more. (The trial will have 80% power to detect at least one individual if the underlying risk is 11% or more and 95% power to detect at least one individual if the underlying risk is 19% or more).

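### The condition for running ADCI names no arm, visit or Day 0 reference and is absent from the body of the protocol; read literally, the 15 controls dilute it

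*Protocol*

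**What the plan says.** The synopsis states the condition twice, under the exploratory objectives and again under the exploratory evaluation criteria: ADCI is performed "only if isotype study shows the production of MSP3 specific cytophilic Abs in > 30% of volunteers". Neither place says which arm is counted, at which visit, against what baseline, or what level counts as positive.

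The body of the protocol has no such condition. Section 2.3 lists evaluation of IgG function by ADCI as an objective without qualification. Section 15.3.2 says that the functional assays "will be done on samples obtained on the following days: D0, D84, D168 and D365".

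The synopsis gives the size of the trial: "The total number of participants will be 45 allocated in two groups as following". Section 16.2 splits it into "15 receiving 15µg MSP 3 vaccine", "15 receiving 30µg MSP 3 vaccine" and "15 receiving Hepatitis B vaccine".

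On baseline antibody, section 15.1.2 says that "it is anticipated that almost all participants will be sero-positive before vaccination occurs". For that reason it drops the sero-conversion rate and uses ratios to D0 for IgG and IgM. Section 15.1.1 has the IgG1 to IgG4 isotypes measured at D0 as well as after vaccination.

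**The concern.** There are two defects. First, a team following the synopsis and a team following section 15.3.2 would act differently on the same isotype results: one might skip ADCI, the other would run it.

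Second, the rule pools arms. Taken at its word, *volunteers* covers every child in the trial, so a third of the denominator never received MSP3. An antibody response confined to MSP3 recipients then has to be well above 30% among them before the assay is run.

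At stake is the trial's only parasite-inhibition assay, and the mechanism that the background section gives as the reason for selecting this antigen. There is also a lesser concern in the other direction: with no D0 reference, antibody from natural exposure might be counted.

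**Working it through.** **The plan's own figures.** The 30% threshold has no derivation in the protocol. The only calculated figures are in section 16.2: the probability of at least one event among 14 children, 1 − (1 − p)^14. This gives 0.897 at p = 15%, 0.804 at 11% and 0.948 at 19%, against the stated 90%, 80% and 95%. They reproduce but do not bear on the ADCI condition.

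**Inputs from section 16.2.** 15 + 15 = 30 MSP3 recipients and 15 controls, 45 in all. The rates of cytophilic response and of background positivity are not in the documents; the values below are assumptions.

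**Threshold.** 0.30 × 45 = 13.5, so at least 14 positives are needed (14/45 = 31.1%; 13/45 = 28.9% fails). With no positive controls, all 14 must come from the 30 MSP3 recipients: 14/30 = 46.7%. Among MSP3 recipients alone, 0.30 × 30 = 9, so strictly more than 30% means at least 10 (33.3%). With 10 to 13 responders of 30 (33.3% to 43.3%), the vaccinees pass 30% but the pooled share is only 22.2% to 28.9%, and the condition fails.

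**Dilution.** For true response rate v in MSP3 recipients and c in controls, P(met, pooled) = P(Bin(30, v) + Bin(15, c) ≥ 14), and P(met, MSP3 only) = P(Bin(30, v) ≥ 10).

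| v | Pooled, c = 0 | Pooled, c = 10% | MSP3 recipients only |
|---|---|---|---|
| 35% | 0.13 | 0.29 | 0.64 |
| 40% | 0.29 | 0.49 | 0.82 |
| 45% | 0.50 | 0.69 | 0.93 |
| 50% | 0.71 | 0.84 | 0.98 |
| 60% | 0.95 | 0.98 | 0.999 |

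Dropout changes little. Section 16.2 counts 14 completers per MSP3 arm; if controls also fall to 14 (an assumption), 13 of 42 are needed, that is 13/28 = 46.4% of MSP3 recipients. At c = 0 the pooled probabilities are then 0.14, 0.31 and 0.51 at v = 35%, 40% and 45%.

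**Natural exposure, if presence counts.** With an inert vaccine and background prevalence b in all arms, P(met) = P(Bin(45, b) ≥ 14): 0.05 at b = 20%, 0.22 at 25%, 0.49 at 30%, 0.92 at 40% and 0.997 at 50%. Restricting the count to MSP3 recipients without a D0 reference does not cure this: P(Bin(30, b) ≥ 10) is 0.41 at 30% and 0.82 at 40%.

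**The case against.** *Production may mean a rise.* In the synopsis the isotypes sit under an objective about antibody levels going up, and the main humoral results are ratios to D0. This is a fair reading, and under it pre-existing antibody does not count. It does not settle the arm, the visit or the size of rise. With first injections in March, D84 falls from late May to late June and D168 from mid-August to mid-September. Much of that is inside the June to October transmission peak given in the epidemiology section, so natural boosting could still count.

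*Almost everyone is sero-positive, so the gate is bound to open.* A reader might infer this from section 15.1.2. The documents do not support it. That statement concerns anti-MSP3 antibody generally, not cytophilic isotypes. The introduction says that in unprotected people these antibodies are mostly of the non-cytophilic kind, so the background in children aged 1 to 2 years may be low.

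*An open gate would be taken as proof of a vaccine effect.* Nothing in the protocol makes the gate a result. ADCI includes D0 samples, and section 4.1 compares vaccinees with controls, so running the assay unnecessarily misleads nobody.

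*Volunteers may mean MSP3 recipients, and details may be in the analysis plan.* The word is used elsewhere for both groups, and a formal reporting and analysis plan is announced. A positivity cut-off could reasonably be left there. That does not remove the conflict between the synopsis and the body.

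*A closed gate loses little.* Plasma is frozen, isotypes are still reported, and Western blot, also listed among the exploratory functional tests, is not conditional. This stands and limits the severity. Western blot, however, shows recognition of the native protein, not parasite inhibition.

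*A pooled count protects the blind.* An independent statistician already prepares unblinded safety reports and could compute an arm-specific proportion.

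**Conclusion.** The point holds, at low severity. The protocol contradicts itself on whether ADCI is conditional; this rests on the text alone. On the literal reading of the denominator, the 30% hurdle becomes 47% of MSP3 recipients when no control is positive, and a true response of 35% to 45% would meet it with probability 0.13 to 0.50, against 0.64 to 0.93 if only MSP3 recipients were counted. The loss shrinks as the response rises or as more controls are positive; at a 60% response it is about 5 points.

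Opening through natural exposure is the lesser problem. It needs presence rather than a rise to count, and a cytophilic background of roughly 30% or more, for which the documents give no figure. The two failures should not be added together: dilution needs few positive controls, and spurious opening needs many.

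No primary, secondary or safety conclusion depends on this rule. ADCI is exploratory, section 16.4 makes the analysis descriptive, and the go/no-go decision looks only at safety data.

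**What to change.** Use one wording in the synopsis and in section 15.3.2, choosing one of two options.

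- Delete the condition, so that ADCI is run as section 15.3.2 already says. The cost is possibly more ADCI assays.
- Keep a condition, but tie it to vaccine response. For example: ADCI is performed if more than 30% of MSP3 recipients with both D0 and D84 samples show a D84/D0 rise in IgG1 or IgG3 to MSP3-LSP above a fold threshold fixed in advance. The independent statistician computes the proportion so that the blind is kept, and the control proportion is shown alongside. The cost is fixing the threshold beforehand, for instance from assay variability.

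Either way the edit is about two sentences. The second option uses samples already planned under section 15.1.1. Section 15.1.3 gives a different list of isotype days (D112, D140 and D252, with no D84), so the two lists must be reconciled for the D84 value to be assured.

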# Trial Objectives

## Primary Objective

**To assess the safety and reactogenicity** of 3 doses of 15 µg and 30 µg MSP3 LSP adjuvanted in Aluminium hydroxide given at D0, D28 and D56 in healthy children 1-2 years old in Burkina Faso on the following:

1. Immediate reactogenicity (within 1 hour, with emphasis on allergic reactions),
2. Local and systemic reactogenicity during the 7 days following the vaccine administration(day of vaccination and 6 subsequent following days)
3. Unsolicited adverse events occurring within 28 days following each vaccination
4. Serious adverse events (SAE) throughout the study period.

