|  | **SCREENING** | | | | | | | **VACCINATION** | | | | | | | | | **LONG TERM SAFETY FOLLOW UP** | | |  |
|  |  | | | | | | | **DOUBLE-BLIND PHASE** | | | | | | | | | **SINGLE-BLIND PHASE** | | |  |
|  |  | | | | |  |  |  |  | |  | |  | |  | |  |  | |  |
| **BS;** Blood Sample. **Vacc;** Vaccination. | | | | | | | | | | | | | | | | | | | | |
|  | | | | | | | | | | | | | | | | | | | | |

- Double blind (observer blind, participant blind), randomized, controlled, dose escalation, Age de-escalation, phase Ib study
- One study centre,
- Two parallel groups
- Group 1: 23 subjects (15 subjects receiving MSP-3 vaccine 15 µg and 8 subjects receiving Hepatitis B vaccine).
- Group 2: 22 subjects (15 subjects receiving MSP-3 vaccine 30 µg and 7 subjects receiving Hepatitis B vaccine)
- Immunization schedule will be 0, 1, and 2 months for all cohorts and provisionally as following for each group:
  - Study days 0, 28 and 56 for group 1
  - Study days 14, 42, 70 for group 2
- Vaccinations of groups 1 and 2 will be staggered: immunization in group 2 will start 2 weeks after group 1. This interval may be extended if deemed necessary due to SAEs or other safety concerns.
- Randomization will be done for each group at the times of first vaccinations.
- Route of inoculation will be by subcutaneous injection into right or left deltoid (alternately).
- Each child will be observed for at least 60 minutes after vaccination to evaluate and treat any acute adverse events (AEs)
- Study duration will be approximately 13 months per subject.
- Seven (7) day follow-up period for solicited adverse events (day of vaccination plus 6 subsequent days)
- Twenty eight (28) day follow-up period for unsolicited adverse events (Vaccination day plus 27 subsequent days)
- Follow-up of serious adverse events (SAE’s) for 12 months after the first dose of study vaccine (9 months after dose 3)
- At the end of the follow-up period for unsolicited AEs (i.e., one month after the third dose), subjects will be followed by field workers at home at monthly intervals to record SAEs.
- Data collection: conventional Case Report Form (CRF).

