## Contraindications to subsequent vaccination

### Indications for deferral of vaccination

The following AEs constitute contraindications to administration of MSP3 or Hepatitis B vaccines at that point in time; if any one of these AEs occurs at the time scheduled for vaccination, the subject may be vaccinated at a later date, within the time window specified in the protocol, or withdrawn at the discretion of the investigator. AEs should be followed-up accordingly:

- Acute disease at the time of administration of investigational product (acute disease is defined as the presence of a moderate or severe illness with or without fever). All vaccines can be administered to persons with a minor illness such as diarrhea or mild upper respiratory infection without fever, i.e. axillary temperature < 37.5°C.
- Axillary temperature of  37.5°C.

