## Unsolicited symptoms

Unsolicited symptom is defined as any adverse event (AE) reported in addition to those solicited during the clinical study. Also any “solicited” symptom with onset outside the specified period of follow-up for solicited symptoms will be reported as an unsolicited adverse event.

Unsolicited symptoms will be recorded from the first dose of vaccination to 30 days post third dose.

For the unsolicited symptoms, intensity will be assessed as follows:

| Mild | Easily tolerated by the subject, causing minimal discomfort and not interfering with everyday activities. |
| --- | --- |
| Moderate | Sufficiently discomforting to interfere with normal everyday activities. |
| Severe | Prevents normal, everyday activities. |

Outcome and causal relationship will be assess as described in section 13.4.2.3 and 13.4.2.4

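### The protocol gives conflicting follow-up periods for unsolicited events in the primary endpoint, and the per-dose version leaves a short gap whenever a dose is deferred for illness

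*Protocol*

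**What the plan says.** The protocol describes the period for unsolicited events in several places:

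- **Synopsis, Primary Evaluation Criteria:** "Occurrence of unsolicited symptoms during a 28 day follow-up period after each vaccination". The Primary Objective, in the synopsis and in the body, says much the same: "Unsolicited adverse events occurring within 28 days following each vaccination".
- **Study Design Overview:** this section fixes the day count: "Twenty eight (28) day follow-up period for unsolicited adverse events (Vaccination day plus 27 subsequent days".
- **Section 13.4.2.4 (Assessment of Outcome):** an unsolicited event is a non-serious event within 30 days after vaccination.
- **Section 14.1 (Definition of the Criterion, under Primary evaluation criteria):** there is no per-dose period. Events count up to one month after the third dose, but only if they occur outside scheduled visit times and require a physician visit.
- **Section 14.2.2 (Unsolicited symptoms):** "Unsolicited symptoms will be recorded from the first dose of vaccination to 30 days post third dose".

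Two further provisions matter. The dosing schedule is "Primary immunisation : day 0, 28; and 56", with a 4-day window at each dosing visit in the synopsis schedule table. Section 8.5.1 says that when a child has an acute illness or fever on the planned day, "the subject may be vaccinated at a later date, within the time window specified in the protocol, or withdrawn at the discretion of the investigator". Nothing states which definition of the unsolicited period governs the primary endpoint.

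**The concern.** Periods of 28 days starting at each injection have no slack when injections are planned 28 days apart. Any deferral opens a gap between the end of one period and the start of the next, and the gap opens because the child is ill. A non-serious illness starting in the gap would be recorded under section 14.2.2 but would belong to no period under the synopsis and the Study Design Overview.

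Section 14.1 does not clearly rescue it. Read literally, an illness found at the scheduled vaccination visit is not outside scheduled visit times. Two of the written forms of the criterion can therefore miss the same event, and two analysts working from this protocol could report different primary endpoint counts from the same data.

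**Working it through.** The protocol prints no figure for this point, so there is none to reproduce. The check is a day count.

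**Inputs**
- Planned doses on D0, D28 and D56 (synopsis, Vaccination Schedule).
- Window of 4 days at each dosing visit (synopsis schedule table). Its sign does not survive in the available text; a late dose needs only +4.
- Deferral within the window for illness or fever (section 8.5.1).
- Last covered day after an injection: +27 (Study Design Overview), +28 (a literal reading of within 28 days following, in the Primary Objective) or +30 (section 13.4.2.4).

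**Formula.** With a dose on day a, the next on day b, and coverage through a + L, the uncovered days run from a + L + 1 to b − 1. Their number is max(0, b − a − L − 1).

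| Doses | L = 27 | L = 28 | L = 30 |
|---|---|---|---|
| D0, then D28 (on time) | 28 − 0 − 27 − 1 = 0 | 0 | 0 |
| D0, then D32 | 32 − 0 − 27 − 1 = 4 (D28–D31) | 3 (D29–D31) | 1 (D31) |
| D28, then D60 | 60 − 28 − 27 − 1 = 4 (D56–D59) | 3 (D57–D59) | 1 (D59) |

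Under the continuous span of section 14.2.2 there are 0 uncovered days between doses, whatever the deferral.

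**Which illnesses can fall in the gap?** An illness that defers a D28 dose is present on D28, so it began on D28 or earlier. With the earlier dose on time:
- Onset before D28: inside the dose 1 period on every count.
- Onset on D28: outside at L = 27, inside at L = 28 or 30.
- A second illness starting during the deferral: outside at L = 27; outside at L = 28 or 30 only if it starts on the uncovered days in the table.

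**Share that began earlier (assumption).** With a steady onset rate and geometric durations of mean m days, the share of illnesses present on a given day that began that day is 1/m. For m = 3 to 5 days this is 1/3 to 1/5, so about 67% to 80% began earlier and are counted even at L = 27.

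**Effect on children counted (assumption).** The protocol gives no illness rate. At an assumed 4 to 12 illnesses per child-year, the chance of at least one in 84 days is 1 − exp(−4 × 84/365) = 60% to 1 − exp(−12 × 84/365) = 94%. Most children who lose one episode would thus still count as having had an event. Simulating 45 children under these rates and durations gave an expected 0.08 to 0.43 children whose yes/no status changes at L = 27, and essentially none at L = 28.

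**The case against.** The strongest reply is that section 14 is the section headed as the primary evaluation criteria, that it sets no per-dose period, and that section 14.2.2 records without a break. On that view the per-dose phrase in the synopsis is shorthand and nothing is lost. This partly stands: the data will exist, and it would be wrong to say that the protocol counts unsolicited events only in per-dose periods. It does not settle the matter. The objective and the synopsis criteria say something different, no order of precedence is given, and section 14.1 carries its own restriction.

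It can also be said that the full 4-day gap depends on one parenthesis in the Study Design Overview. That is correct. On a day +28 count a deferring illness that starts on the planned day is covered if the earlier dose was on time, and only a second illness during the deferral can be missed.

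A reader might infer several stronger things that the documents do not support:
- **That deferring illnesses are generally lost.** Most probably begin before the planned day, and serious events are counted throughout the study.
- **That a lost event is worth 6.7 percentage points (1/15) in an arm, with a 43% to 91% chance of losing at least one.** These figures rest on illness rates with no source in the protocol. They also count episodes, not children whose status changes.
- **That gaps of 8 days, or events counted for two doses, will occur.** Both need a window that allows early dosing, and its sign is not legible. Nor does the protocol say that an overlapping event counts twice.
- **That the reports to the safety board lose events.** The Safety monitoring reports section asks for all unsolicited events after doses 1 and 2 and states no 28-day cut-off.

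**Conclusion.** The point holds as an inconsistency in the primary endpoint, not as a demonstrated loss of safety data. The per-dose 28-day wording, the 30-day wording, the restricted span in section 14.1 and the continuous recording in section 14.2.2 cannot all define the same endpoint.

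Under the injection-day-plus-27 count, a dose deferred to the end of its window leaves 4 days uncovered (3 at day +28, 1 at day +30). This needs only that the 4-day window allows a late dose, which section 8.5.1 presupposes. The effect on results is likely to be small: the analysis is descriptive, serious events are unaffected, and under the assumed rates fewer than one child in 45 would change status. It is still worth correcting, because the gap is tied to illness and the data needed to close it are already collected.

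**What to change.** Use one definition in the synopsis (Primary Objective and Primary Evaluation Criteria), the Primary Objective in the body, the Study Design Overview, section 13.4.2.4 and section 14.1, matching section 14.2.2: all unsolicited adverse events with onset from the first injection through 30 days after the last injection received. Remove from section 14.1 the restriction to events outside scheduled visits that require a physician visit. An end date of day +27 would close the gap between doses but would discard days that section 14.2.2 records, so it should not be used.

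Tying the end to the last injection received also covers a child who is withdrawn instead of deferred: an illness starting on D28 after a D0 dose lies within D0 to D30. In by-dose tables, assign each event once, to the most recent injection.

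The cost is wording only; no visit, sample or clinical rule changes. The downside is that by-dose periods will differ by a few days between children.
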